## Abstract

**Background:**

Chronic subdural hematoma (CSDH) is a common neurological pathology, especially in older patients. The actual “gold standard” of treatment is surgical evacuation, with various techniques used across neurosurgical teams. Over the years, there has been growing evidence that inflammatory processes play a major role in the pathogenesis of CSDH. In that context, the use of corticosteroids has been proposed alone or as an adjuvant treatment to surgery. However, this practice remains very empirical and there is a need for high-quality-of-evidence studies to clarify the role of corticosteroids in the management of CSDH.

**Methods/design:**

We propose a double-blind, randomized controlled trial comparing methylprednisolone versus placebo in the treatment of CSDH without clinical and/or radiological signs of severity. The treatment will be administered daily for a duration of 3 weeks, at a dose of 1 mg/kg. The primary endpoint will be the delay of occurrence of surgical treatment at 1 month following the introduction of the treatment. Secondary endpoints will include the rate of recourse to surgery, survival rate, quality of life and functional assessments, occurrence of systemic secondary effects and radiological assessment of the response to treatment. This multimodal assessment will be done at 1, 3 and 6 months. Two hundred and two patients (101 per arm) are expected to be included considering our primary hypotheses.

**Discussion:**

This trial started in June 2016; its results may open interesting alternatives to surgery in the management of patients harboring a CSDH, and may provide insights into the natural history of this common pathology.

**Trial registration:**

ClinicalTrials.gov, ID: NCT02650609. Registered on 4 January 2016.

**Graphical Abstract:**

Graphical output of the OBF boundaries.
[figure not shown]

**Electronic supplementary material:**

The online version of this article (doi:10.1186/s13063-017-1990-8) contains supplementary material, which is available to authorized users.

## Background

Chronic subdural hematoma (CSDH) is one of the most frequent neurosurgical pathologies [1, 2]. To date, it has mainly involved older patients, with an annual incidence rate of 15 cases for 100,000 persons aged over 70 years [3, 4]. Considering that the population of patients aged over 65 years old is estimated to increase three-fold by the 2030s [5], and the increasing prescription of anticoagulant or platelet aggregation-inhibiting drugs, more and more practitioners will be confronted with this pathology which thus represents a major public health issue. Surgical evacuation of CSDH is currently the “gold standard” treatment [6]. In an often fragile population, surgical treatment carries significant morbidity at surgical (early recurrence which manifests itself in acute subdural hematoma, infections, intracerebral hematoma) as well as at medical (seizures, acute respiratory disease, urinary tract infections, confusional states, bedsore complications) levels. There is an increased mortality risk until 1 year after surgical evacuation [7], and hospital costs are high, with a very variable length of stay.

Beyond its classic traumatic etiology, the pathophysiology of CSDH involves inflammatory processes so that CSDH can now also be considered as an inflammatory disease. CSDH, therefore, appears to be a self-sustaining process of neoangiogenesis and fibrinolysis, leading to progressive increase in hematoma volume [8–19]. In this context, corticosteroids could represent an alternative treatment for CSDH because of their inhibiting effects on vascular endothelial growth factor, tissue plasminogen activator, interleukin-6, interleukin-8 and platelet-activating factor [20]. However, the scientific literature on the subject is still very limited [21]. In fact, only case reports and preliminary nonrandomized or retrospective studies have suggested the efficacy of steroids alone or as adjuvant therapy to surgery [22–26].

In this context, a double-blind randomized study is mandatory to assess the efficacy of corticosteroids in CSDH. We propose a randomized controlled trial aiming at evaluating the efficacy of corticosteroid treatment in patients with CSDH without clinical or radiological signs of severity. The investigational medicinal product is methylprednisolone, a synthetic glucocorticoid widely used in treating various inflammatory diseases. It is a commonly used drug for which the mechanisms of action, drug interactions and adverse effects are well known. The purpose of this article is to describe the rationale for the study and to reveal the protocol of the SUCRE (Steroids in sUbdural ChRonic hEmatomas) trial.

## Methods/design

### Study design

The proposed study is a prospective, multicenter, double-blind, randomized controlled, (methylprednisolone versus placebo) phase-III superiority trial performed on two parallel groups. The primary objective is to evaluate the efficacy of corticosteroid treatment in patients with CSDH without clinical or radiological signs of severity. Secondary objectives are to assess the effect of methylprednisolone on quality of life evolution, morbidity and mortality, and radiological evolution of the lesions. This trial is registered at ClinicalTrials.gov as NCT02650609. This article has been written following the Standard Protocol Items: Recommendations for Interventional Trials (SPIRIT) guidelines [27] (Additional file 1).

#### Primary endpoint

The primary evaluation criterion is the delay of occurrence of surgical treatment (censored criteria) of the CSDH at 1 month. One month has been chosen for assessing the primary endpoint because most surgical interventions, if needed, are expected to occur during the first month following the diagnosis of CSDH. Patients who are nonevaluable for the primary endpoint (death, loss to follow-up, etc.) will be censored at the date of death or the latest news.

Criteria for recourse to surgery are (one is sufficient): lack of clinical improvement at 1 month, immediate or delayed clinical deterioration, appearance of radiological signs of severity (midline shift >5 mm, uncal transtentorial herniation).

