#### Secondary endpoints

Secondary evaluation criteria are: quality of life assessed by the Short Form 12-item (SF12) scale [28] at 1, 3 and 6 months; time to surgical treatment during the first 6 months (censored criteria); rate of surgical treatment of the CSDH at 1, 3 and 6 months; functional scales: daily living (Instrumental Activities of Daily Living; IADL) [29], cognitive (Mini-Mental State Examination; MMSE) [30] and the modified Rankin Scale [31] at 1, 3 and 6 months; plasma sodium, potassium and fasting glucose at days 0, 7, 14 and 21 and at 1 month; occurrence of adverse events potentially related to methylprednisolone (electrolyte disorders: hypokalemia, metabolic alkalosis, sodium retention (edema), hypertension, congestive heart failure; endocrine and metabolic disorders: Cushing’s syndrome, adrenal insufficiency, glucose disorders (impaired glucose tolerance, diabetes); gastrointestinal disorders: ulcer, perforation, gastrointestinal tract hemorrhage; skin disorders: acne vulgaris, purpura, hematoma, hypertrichosis; neuropsychological disorders: euphoria, insomnia, agitation, confusion, depression; ophthalmological disorders such as glaucoma); survival at 6 months; radiological improvement, defined by reduction of maximal thickness of hematoma and reduction of midline shift evaluated at 1, 3 and 6 months.

Subgroup analyses of all study endpoints will also be performed in subacute (less than 4 weeks old) and chronic (more than 4 weeks old) CSDH, and in patients treated or not treated with anticoagulant or platelet antiaggregant therapy.

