#### Analysis of the primary endpoint

Time to surgical treatment (i.e., the delay of occurrence of surgical treatment) of the CSDH at 1 month will be compared between the two groups with the log-rank test. Two interim analyses after inclusion of one third and two thirds of the patients, and one final analysis are planned. Stopping rules will use the alpha spending function with the O’Brien-Fleming boundary. The cumulative values of alpha for each analysis are: 0.00021 at the first analysis, 0.01202 at the second analysis and 0.04626 at the final analysis (nTerim, V4.0, Statistical Solutions Ltd., Cork, Ireland). The trial will be stopped early if the significance of the log-rank test is below these alpha values.

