#### Analysis of other criteria

Student’s *t* test or a Mann-Whitney test if necessary will be used to compare quantitative variables. Quantitative criteria evaluated several times during the monitoring will be compared with repeated measures analysis of variance (ANOVA) with two factors (time, group). For qualitative criteria, a chi^2^ test will be used. For all these analyses, adjustments can be made in case of heterogeneity at inclusion.

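### Death before surgery is censored like loss to follow-up, and the surgery rates have no stated way to handle it, so an excess of unoperated deaths in either arm can pass for avoided surgery

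*Protocol article*

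**What the plan says.** Under Primary endpoint, the protocol article states: "The primary evaluation criterion is the delay of occurrence of surgical treatment (censored criteria) of the CSDH at 1 month". The same section gives one rule for death and loss: patients who cannot be evaluated for either reason "will be censored at the date of death or the latest news". It also lists clinical deterioration, immediate or delayed, as sufficient on its own for recourse to surgery. Under Analysis of the primary endpoint, time to surgery "will be compared between the two groups with the log-rank test", and the two interim stopping rules act on that same test.

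Secondary endpoints include the "rate of surgical treatment of the CSDH at 1, 3 and 6 months", a separate censored time-to-surgery endpoint over 6 months, and "survival at 6 months". Analysis of other criteria names neither the surgery rates nor survival; its general rule is: "For qualitative criteria, a chi^2^ test will be used". Statistical analysis restricts the analysis to patients who were evaluated, while calling it intention-to-treat. Nowhere does the article treat death before surgery as a failure or a competing event.

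**The concern.** Censoring lets the test speak about the need for surgery only if censored patients would have had the same later risk of surgery as those still followed. Loss for administrative reasons may satisfy this. Death after deterioration does not: by the article's own list that patient qualified for surgery.

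There is room for such deaths. The Background describes a fragile population, and the Discussion admits patients with a GCS score of 13 and leaves the timing of secondary surgery to each investigator. Deaths also need not balance between arms. The article makes mortality a secondary objective, lists gastrointestinal perforation and heart failure among possible drug effects, and cites a retrospective study with fewer deaths on corticosteroids. At stake is whether a lower surgery rate means that surgery was avoided or that patients died before it.

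**Working it through.** **1. The plan's own figure.** Inputs from Study population: 80% versus 60% operated at 1 month, 90% power, two-sided 0.05.
- HR = ln(1 − 0.80)/ln(1 − 0.60) = 1.609/0.916 = 1.756, as stated.
- Freedman events = (1.960 + 1.282)² × ((HR + 1)/(HR − 1))² = 10.507 × 13.278 = 139.5, so 140. Divided by the mean event rate 0.70, this gives 200 patients.
- The article states 142 events and 202 patients. The design reproduces closely, and this point does not disturb it.

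**2. Log-rank test with death censored.** The article gives no death rates, so all of these are assumed. Simulated trials had 101 patients per arm, 80% needing surgery in both arms (no true effect), and one final test at |z| > 1.96.
- *Deaths independent of the need for surgery* (1-month risk 5% vs 0%, 10% vs 0%, 10% vs 2%, 20% vs 2%): two-sided error 4.5 to 5.4%.
- *Deaths among patients about to be operated on, one arm only* (20,000 trials each):

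| Excess deaths | Two-sided error |
|---|---|
| 3 | 5.6% |
| 5 | 7.1% |
| 8 | 9.9% |

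A second simulation (4,000 trials) set the share of would-be surgical patients who die. It gave about 7% error at 5% vs 0%, 9% at 10% vs 0% (about 8 deaths, since 0.10 × 81 ≈ 8), and 23% at 20% vs 2%. Nearly all the added error favours the arm with more deaths.

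**3. Surgery rates by chi-square.** Start from 81/101 (80.2%) operated in each arm and let k would-be surgical patients die unoperated in one arm.
- *Counted as not operated:* k = 5 gives 76/101 = 75.2% (p = 0.40); k = 10 gives 71/101 = 70.3% (p = 0.10); k = 13 gives 68/101 = 67.3% (p = 0.038).
- *Dropped from the denominator:* k = 5 gives 76/96 = 79.2%; k = 13 gives 68/88 = 77.3%. The shift is smaller, but patients are removed by a post-randomisation outcome.
- *Independent deaths, counted as not operated:* operated proportion = λs/(λs + λd) × (1 − exp(−(λs + λd))), with λs = −ln 0.20 = 1.609. For 10% mortality λd = 0.105 and the result is 77.0%; for 2% it is 79.4%. That is a false difference of 2.4 points.

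**4. Cost of counting death as an event.** For an independent 1-month death risk d, equal in both arms, the event proportions are 1 − 0.2(1 − d) and 1 − 0.4(1 − d).

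| d | Placebo | Active | HR | Power at 202 (Freedman) |
|---|---|---|---|---|
| 0% | 80.0% | 60.0% | 1.756 | 90.4% |
| 2% | 80.4% | 60.8% | 1.740 | 89.7% |
| 5% | 81.0% | 62.0% | 1.716 | 88.7% |
| 10% | 82.0% | 64.0% | 1.679 | 86.8% |

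**The case against.** The strongest reply is that censoring at death is not an error in itself. It yields a valid log-rank comparison of the surgery hazard among patients still alive, and the simulation with independent deaths confirms this. Distortion needs deaths that are both tied to imminent surgery and unequal between arms, and the article gives a figure for neither. This stands, and it limits the size of the point.

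The article also has safeguards. Severe cases are excluded, mortality is assessed separately, time to surgery is followed as a censored endpoint to 6 months, and the Data and Safety Monitoring Board can propose stopping for safety. An excess of deaths would therefore be visible. But none of this changes the death rule or says how the two results are to be read together.

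The chi-square reading of the surgery rates is an inference from one general sentence, and a statistical analysis plan that is not shown may settle it. That stands too. The inference matters only because neither way of handling unoperated deaths in a simple proportion is satisfactory.

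A reader might infer three stronger claims that the article does not support:
- *That three unoperated deaths cut power from 90% to 80%*, by comparing 60% with 63% operated. The log-rank test removes those patients from the risk set and does not count them as unoperated to 1 month. Simulated power in that scenario is about 88 to 89% with deaths censored and 82 to 83% with deaths counted.
- *That the bias favours methylprednisolone.* The only mortality comparison cited, a retrospective study of corticosteroids as an adjunct to surgery, reports a three-fold lower risk of death. If that held here, the distortion would tend to work against the active arm.
- *That deaths also flatter an arm on survival.* There a death counts against its arm; only the handling of losses is at issue.

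**Conclusion.** The point holds in a limited form. The article states a rule that treats death before surgery as loss to follow-up, although its own criteria make deterioration a reason to operate. The primary test therefore addresses the cause-specific surgery hazard only, and it can lean towards either arm.

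Under the assumption that deaths fall on patients about to be operated on, the effect is negligible at 3 excess deaths in one arm, about 7% error at 5, and about 9 to 10% at 8. With few, balanced or unrelated deaths there is nothing material. The crude surgery rates are more exposed than the log-rank test, but only if they are analysed as the general chi-square rule suggests. The planned sample size and primary test can stay.

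**What to change.** - Keep the log-rank test on time to surgery as the primary analysis.
- Prespecify a sensitivity analysis of time to surgery or death by 1 month, to be reported beside the primary result.
- Estimate the surgery rates at 1, 3 and 6 months by cumulative incidence (Aalen-Johansen) with death as a competing event, giving between-arm differences and confidence intervals.
- Analyse 6-month survival by Kaplan-Meier and log-rank, so that patients lost to follow-up contribute until they leave.

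The cost is analysis-plan wording and standard code on data already collected, with no extra patients. The downside is one additional analysis to report. Under equal independent mortality of 2 to 10%, it keeps about 87 to 90% power at 202 patients.

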### Study population

Our hypothesis is that 80% of the patients taking placebo will be operated on at 1 month. A total sample size of at least 202 patients (142 events) is required to achieve 90% power to detect a decrease in the rate of surgery to 60% (hazard ratio of 1.756) with methylprednisolone, using a two-sided log-rank test with a 0.05 significance level assuming that the hazards are proportional (nTerim, V1.1, Statistical Solutions Ltd., Cork, Ireland).

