#### Follow-up

Patients are followed up for a period of 6 months, and are evaluated at 1, 3 and 6 months. At days 0, 7, 14 and 21 and at the 1-month visit, plasma sodium, potassium and fasting glucose are measured. Fasting plasma cortisol at 8 a.m. is measured 2 days after the end of the treatment with corticosteroids (at day 23). Patients will undergo interval cerebral CT scans to evaluate their CSDH at the following intervals: screening visit, M1, M3 and M6 (Fig. 1). This biological surveillance allows the detection of any electrolyte or glycemic impairment that could occur with steroid treatment.

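### The primary endpoint closes at 1 month, the point at which lack of improvement becomes a trigger for surgery, and the plan does not say whether operations decided at that visit count as events

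*Protocol article*

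**What the plan says.** All references are to the protocol article.

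- **Primary endpoint, horizon:** "The primary evaluation criterion is the delay of occurrence of surgical treatment (censored criteria) of the CSDH at 1 month". The Abstract starts the clock at the introduction of treatment. One month was chosen because "most surgical interventions, if needed, are expected to occur during the first month following the diagnosis of CSDH".
- **Primary endpoint, triggers:** "Criteria for recourse to surgery are (one is sufficient): lack of clinical improvement at 1 month, immediate or delayed clinical deterioration". New radiological signs of severity are a further trigger.
- **Primary endpoint, censoring:** "Patients who are nonevaluable for the primary endpoint (death, loss to follow-up, etc.) will be censored at the date of death or the latest news". No other censoring rule is given.
- **Follow-up:** clinical evaluations are at 1, 3 and 6 months. For imaging, "Patients will undergo interval cerebral CT scans to evaluate their CSDH at the following intervals: screening visit, M1, M3 and M6".
- **Study population:** "Our hypothesis is that 80% of the patients taking placebo will be operated on at 1 month". The trial is sized "to detect a decrease in the rate of surgery to 60% (hazard ratio of 1.756) with methylprednisolone". "A total sample size of at least 202 patients (142 events) is required to achieve 90% power".
- **Authorized and unauthorized medicinal products:** lack of clinical improvement, with no time point attached, is a treatment failure for which surgery should be considered.
- **Discussion:** the timing of secondary surgery is left to each investigator.
- **Secondary endpoints:** time to surgery over 6 months, and surgery rates at 1, 3 and 6 months.

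**The concern.** One route to surgery, as worded in the Primary endpoint section, can be satisfied only when the primary follow-up ends. A second route, new radiological severity seen on a scheduled scan, also first becomes visible at M1. A patient who is judged not improved at M1 and operated on some days later has failed by the plan's own criteria, yet would enter the log-rank test as not operated.

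Two patients with the same clinical course could therefore be classified differently because one was seen two days earlier, or because one centre had a theatre slot sooner. That is noise in the primary event. If such operations were part of what the planners had in mind for the 80% and 60%, the event count and the contrast between arms are both smaller than planned. The 6-month secondary endpoint captures these operations, but the confirmatory test does not.

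**Working it through.** **1. Reproduce the planned size.** Inputs from Study population: 80% on placebo, 60% on methylprednisolone, two-sided 0.05, 90% power, proportional hazards.

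- Hazard ratio = ln(0.20)/ln(0.40) = 1.756, as stated.
- Freedman events = (1.960 + 1.282)² × ((1 + HR)/(1 − HR))² = 139.5, so 140.
- Patients = 140/0.70 = 200.
- The article gives 142 events and 202 patients, so the basis is reproduced closely.
- At 202 patients, expected events = 101 × (0.80 + 0.60) = 141.4, and power = Φ(√141.4 × 0.756/2.756 − 1.960) = 90.4%.
- Since 142/202 = 70.3%, almost exactly the mean assumed event rate, there is no visible reserve.

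**2. Remove a late share.** Let f be the share of the operations in the 80% and 60% that are decided at M1 and performed after the cut-off. The article gives no value, so f is an assumption. Here it is equal in both arms. For f = 10%:

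- Rates: 0.80 × 0.90 = 72% and 0.60 × 0.90 = 54%.
- HR = ln(0.28)/ln(0.46) = 1.639.
- Events = 101 × (0.72 + 0.54) = 127.3.
- Power = Φ(√127.3 × 0.639/2.639 − 1.960) = 78.0%.

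| f | Rates | HR | Events | Power, formula | Power, simulated, late operations censored | Power, simulated, counted at M1 |
|---|---|---|---|---|---|---|
| 0 | 80% vs 60% | 1.76 | 141 | 90.4% | about 91% | – |
| 5% | 76% vs 57% | 1.69 | 134 | 84.5% | – | – |
| 10% | 72% vs 54% | 1.64 | 127 | 78.0% | 80–84% | 88–91% |
| 20% | 64% vs 48% | 1.56 | 113 | 64.6% | 66–70% | 84–88% |
| 30% | 56% vs 42% | 1.51 | 99 | 52.1% | 53–57% | 83–86% |

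The simulated columns are the range over log-rank simulations with 101 patients per arm and exponential times within the month. Some used a single look at 0.05. Others used the three planned looks at 67, 135 and 202 patients with the article's thresholds of 0.00021, 0.01202 and 0.04626.

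**3. Vary the assumptions.**

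- *Late operations come on top of the 80% and 60%.* The in-window rates are unchanged, and power stays near 90%.
- *Events are lost but the hazard ratio stays at 1.756.* Power is 87.2%, 83.1% and 77.9% for 10%, 20% and 30% fewer events.
- *Late operations only on placebo (72% vs 60%).* HR = ln(0.28)/ln(0.40) = 1.389, and power is 46.9%.
- *Late operations only on methylprednisolone (80% vs 55%).* HR = ln(0.20)/ln(0.45) = 2.016, and power is 97.6%.

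The power of the primary test is therefore sensitive to a quantity that the article leaves open, and the direction of the change depends on how late operations split between the arms.

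**The case against.** A reader might infer that operations decided at M1 are certainly censored, that the planned rates cannot be reached, and that power must fall. The article supports none of these outright.

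- **Censoring is inferred.** The only explicit rule covers death, loss to follow-up and the like. A condensed article commonly leaves the exact cut-off day and visit window to the full protocol or analysis plan, and same-day surgery at M1 might count.
- **Surgery for non-improvement need not wait for M1.** Another section gives that trigger without a time point, and the Discussion leaves timing to investigators. Imaging is not restricted to the scheduled scans, and clinical deterioration is a separate trigger that needs no M1 scan.
- **The 80% and 60% may already mean operations performed by 1 month.** That is the plain reading of the sample-size sentence, and it fits the stated reason for the horizon. M1-decided operations would then be additional, and the planned power would hold.
- **Validity is not shown to be at risk.** A common horizon under double blinding does not by itself bias the log-rank test or inflate type I error, and the 6-month endpoint picks up later operations.

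All four points stand, and they make the size conditional. They do not remove the conflict. The trigger and the horizon are both stated, in the same section, at the same time point, so this is more than a detail left for later. That other sections time the same trigger differently adds to the uncertainty about which operations fall inside the window.

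**Conclusion.** The concern holds in a conditional form. As written, the primary endpoint stops where one of its own routes to surgery begins. An operation decided at M1 and performed shortly afterwards would be left out of the primary test, and whether it is left out would depend on scheduling.

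The loss of power rests on two assumptions that the article does not settle: that the 80% and 60% include such operations, and that their share is similar in both arms. If both hold, power falls from about 90% to roughly 78–84%, 65–70% or 52–57% at late shares of 10%, 20% and 30%. If the first fails, planned power stands. If the second fails, power can go down or up. No likely value of the late share can be derived from the article, so an unconditional statement that the trial is underpowered would not be supported.

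**What to change.** Leave patient care as it is and define the event:

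1. State the cut-off in days from the start of treatment, and a window for the M1 visit.
2. Besides operations performed by the cut-off day, count as a primary event any operation whose decision was recorded on or before the M1 visit within its window. Date it at the earlier of the operation and the cut-off day.
3. Record both the decision date and the operation date on the case report form.
4. Add a sensitivity analysis using actual operation dates only, and keep actual dates for the 6-month secondary endpoint.
5. State whether the 80% and 60% include operations decided at M1.
6. Settle all of this before the first interim analysis, so that the rule cannot be chosen in the light of results.

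The Primary endpoint section, the section on authorized and unauthorized medicinal products, and the Discussion time surgery for lack of improvement differently and must be reconciled. No clinical rule is proposed here.

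The cost is a paragraph of text, one extra date and one sensitivity analysis. The downside is small: a decision date is less objective than an operation date, which is why the sensitivity analysis belongs with it.
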